##### Statistical analysis

Statistical analysis will be performed using an intention-to-treat (ITT) approach. Baseline infant and mother demographics and clinical characteristics will be summarized between milk and placebo groups using a chi-square or Fisher exact test for categorical variables (i.e. infant gender, race/ethnicity, socioeconomic status, maternal diagnosis of pre-eclampsia, premature and/or prolonged rupture of membranes, delivery mode, and steroid administration) and an independent *t* test or a Wilcoxon two-sample test for continuous variables (i.e. the time of initial exposure to mother’s own milk, duration [number of days] of central line placement and mechanical ventilation, gestational age, birth weight, post-natal steroids, antibiotic duration), depending on satisfying the normality assumption or not, respectively. A multivariable logistic regression with L-OS or NEC or death as the dependent variable, and group (milk versus placebo) as the primary independent variable will be constructed to assess the strength of association between oropharyngeal milk treatment and risk of L-OS or NEC or death, adjusting for pre-specified covariates including sex, gestational age and birth weight. Odds ratios and corresponding 95 % confidence intervals will be reported. Because the amount of mother’s milk that enrolled infants receive as a “feeding” will affect our study endpoints, we will closely monitor and record the total amount of mother’s milk received (percent of total feeding volume) for each study subject. We do not anticipate the amount of milk the infant receives as an enteral feed will be affected by group assignment. However, if we do observe a significant difference between the intervention and placebo groups, we will control for this variable in the regression models. While the main hypotheses will be tested using ITT analysis, we will also conduct per protocol analysis only for patients who complete the treatment. Completed treatment is defined as (the infant) having received 70 % of planned doses. However, this will be considered supplemental and exploratory, and the results will not be used as main conclusions of the study.

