#### Randomization

A 1:1 blocked randomization scheme was utilized to yield “comparable” subjects in each of the 2 groups, stratified by birthweight (<750 g, 751–999 g, 1000–1250 g) within each site, to avoid imbalance in the distribution of the 2 groups at each site. We produced a separate block randomization list within each site for each subgroup (a total of three strata). The randomization is based on permutated blocks with random sizes varying from 2 to 4 (to avoid guessing) to make sure that each site will have an equal number of participants in each group. The randomization list was generated prior to study initiation using a random seed number via SAS PROC PLAN (SAS Inc., Cary, NC, USA) to generate the stratified randomization design. The statistician prepared sealed, numbered opaque envelopes for each site, with randomization assignment inside. The envelopes were given to the site’s research coordinator who assures that they are used in numerical order. After informed consent is obtained, the research coordinator opens an envelope, removes the group assignment form, writes the infant’s study ID # and date on the form, makes a copy of the form and sends it to the statistician, keeping the original in the infant’s study file. Group A (treatment) infants receive OMM, while Group B (control) infants receive a placebo (sterile water). In the case of a multiple birth, twins are stratified and randomized into either the intervention or the control group, and will be analyzed independently between the two experimental groups. Triplets or higher order multiple births are not be eligible for the study.

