##### Sample size/Power analysis

We hypothesize that extremely premature infants who receive oropharyngeal administration of mother’s milk will have a significantly lower incidence of L-OS (primary endpoint). Based on recent (2012) data from the Vermont-Oxford Network that included > 20,000 ELBW infants, the incidence of L-OS in this population was 19.4 %. Based on data from Manzoni et al. [14], that showed a reduction of L-OS from 17 % to 6 % with exogenous bovine lactoferrin in preterm infants, we conservatively estimate a reduction in L-OS from 20 % to a total of 10 % in milk-treated infants. Since Manzoni et al. [14] used a lactoferrin dose similar to that in mother’s milk, and based on studies that mother’s milk reduces L-OS [6–8] this effect size of reduction (from 20 % to 10 %) should be realistic and obtainable given the patient population. Since many variables may alter the risk for L-OS in extremely premature infants multivariable logistic regression (for dichotomous L-OS outcome) will be performed adjusting for covariates such as sex, gestational age and birth weight. Power calculations were determined using PASS 14.0 software (NCSS, LLC, Kaysville, UT, USA). We estimate that up to a total of 10 covariates will account for a combined 20 % (*R*^*2*^ = 0.2) of variance in the regression model. Based on a 2-tailed alpha of 0.05 and 80 % power, a sample size of 498 (249 in each group) will be needed to reach a statistical power of 80 % to detect a difference of 10 % versus 20 % (effect size odds ratio (OR) = 0.44) in L-OS outcome between milk and placebo groups. Therefore, the study is adequately powered for the primary endpoint L-OS. The study sample is being accrued from 5 sites and, based on a lactation initiation rate of > 70 % for all sites (conservative, based on actual rates of 80–90 %), and an estimated refusal rate of 30 % (a conservative estimate based on our previous experience in recruiting subjects for this intervention), we will screen a total of 1270 patients to enroll 622, with an estimated dropout rate of 20 %, that will allow us a complete analysis for 498 subjects.

##### Outcome measures for specific Aim 1

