Primary endpoints: L-OS is defined as the new onset of at least 2 clinical symptoms with a positive blood culture (noted after Day of life 3) and identification of an organism known to be a cause of sepsis rather than a contaminant. If the blood culture shows a potential contaminant (such as *Staphylococcus epidermidis*) a second blood culture is obtained to confirm the presence of bacteremia.

Secondary endpoints: NEC and death. NEC is defined according to modified Bell’s criteria stage > 2 with clinical signs and radiological evidence including any of the following: pneumatosis intestinalis, portal venous gas with or without pneumoperitoneum.

Covariates: sex, gestational age and birth weight will be included as covariates.

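### Randomisation is stratified by birth weight within site, but site is not among the covariates stated for the L-OS, NEC and death models

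*Protocol article*

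**What the plan says.** Protocol article, Randomization: allocation is 1:1 in permuted blocks, "stratified by birthweight (<750 g, 751–999 g, 1000–1250 g) within each site, to avoid imbalance in the distribution of the 2 groups at each site". Each site has its own list for each birth-weight band, so five sites and three bands give 15 cells. The blocks are "permutated blocks with random sizes varying from 2 to 4 (to avoid guessing) to make sure that each site will have an equal number" of infants in each group.

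Three places describe the covariates:

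- **Sample size/Power analysis** gives sex, gestational age and birth weight as examples, and allows for up to 10 covariates with a combined R² of 0.2.
- **Outcome measures for specific Aim 1** is closed: "sex, gestational age and birth weight will be included as covariates".
- **Statistical analysis** describes a logistic regression on group for L-OS, NEC or death, "adjusting for pre-specified covariates including sex, gestational age and birth weight".

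None of these names site as a covariate, stratum, random effect or cluster term. Analysis of safety endpoints adds Poisson models that reuse the same covariates where applicable.

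**The concern.** When allocation is balanced within site and site predicts the outcome, the two arms have nearly the same site mix. Differences between sites then largely cancel out of the treatment comparison. A model that omits site does not credit this cancellation, so its test is somewhat conservative. In logistic regression, omitting a prognostic factor also moves the estimated odds ratio toward 1 relative to the within-site odds ratio.

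It is plausible that site matters here. The Background links L-OS to central lines, antibiotic use, delayed feeding and unit conditions, and the Oropharyngeal administration procedure leaves feeding to the attending physician. The article does not, however, state that L-OS differs between its sites. What is at stake is some efficiency and a clean match between design and analysis.

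**Working it through.** **1. The plan's own figure.** Inputs from Sample size/Power analysis: 20 % versus 10 %, two-sided alpha 0.05, power 80 %, R² = 0.2.

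- Per arm: n = [1.96·√(2·0.15·0.85) + 0.842·√(0.2·0.8 + 0.1·0.9)]² / 0.10² = 198.96, a total of 397.9.
- Inflated for covariates: 397.9 / (1 − 0.2) = 497.4, rounded up to 498. This matches the plan.
- Odds ratio: (0.1/0.9) / (0.2/0.8) = 0.444. This matches.
- Dropout: 498 / 0.8 = 622.5, against 622 stated.

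**2. Does adding site change the sample size?** Four site indicators plus sex, gestational age and birth weight make 7 covariates, within the allowance of 10. So 498 and 622 stand. Expected L-OS events are 249 × (0.20 + 0.10) ≈ 75 among 498, or 311 × 0.30 ≈ 93 among 622.

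**3. Approximate type I error without site.** The article gives no site rates, so five equal sites with evenly spaced rates around 20 % are assumed. The ratio of true to assumed variance is the mean of p(1 − p) over sites, divided by 0.20 × 0.80 = 0.16. The actual level is 2·[1 − Φ(1.96/√ratio)].

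- Rates 10, 15, 20, 25, 30 %: mean of (0.0900, 0.1275, 0.1600, 0.1875, 0.2100) = 0.1550. Ratio 0.969, level 4.6 %.
- Rates 5, 12.5, 20, 27.5, 35 %: mean of (0.0475, 0.1094, 0.1600, 0.1994, 0.2275) = 0.1488. Ratio 0.930, level 4.2 %.
- All sites alike: ratio 1, level 5 %.

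**4. Simulation under the same assumptions** (N = 500, five equal sites, true odds ratio 0.444 for power and SE):

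| Site rates | Type I without / with site | Power without / with site | SE of log OR without / with site |
|---|---|---|---|
| 10–30 % | 4.9 % / 5.3 % | 86.7 % / 87.7 % | 0.265 / 0.269 |
| 5–35 % | 4.3 % / 4.7 % | 86.4 % / 87.8 % | 0.263 / 0.272 |

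The power difference is 1.0 and 1.4 points. The standard error rises when site is added. Power still improves because the estimate moves further from zero.

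**5. Simulation closer to the design** (N = 498, five unequal sites, three weight bands, blocks of 2 or 4, all three stated covariates in both models, 3,000 runs per setting). Between-site spread is an assumed SD of the log odds. Simulation error is about 0.4 points for type I error and 0.6 for power.

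| SD | Type I without / with | Power without / with | Mean log OR without / with |
|---|---|---|---|
| 0 | 5.2 % / 5.3 % | 89.6 % / 89.7 % | −0.84 / −0.84 |
| 0.3 | 5.0 % / 5.3 % | 89.5 % / 90.0 % | −0.82 / −0.84 |
| 0.6 | 4.3 % / 4.8 % | 87.4 % / 88.7 % | −0.79 / −0.84 |
| 1.0 | 4.0 % / 5.5 % | 87.1 % / 89.7 % | −0.73 / −0.84 |

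At SD 1.0 the attenuation is from an odds ratio of exp(−0.84) = 0.43 to exp(−0.73) = 0.48. Power exceeds the planned 80 % in every row because 249 per arm already gives about 88 % for 20 % versus 10 %, before the R² allowance.

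**The case against.** **Site is unlisted, not excluded.** The wording in Statistical analysis and in Sample size/Power analysis is open (*including*, *such as*), up to 10 covariates are allowed and three are named, and a full analysis plan may list site. A reader might infer that the trial has decided against site, and the documents do not support that. What remains is that the list under Outcome measures for specific Aim 1 has no open wording. Statistical analysis also goes as far as a conditional adjustment for the share of mother's milk in feeds, yet does not mention a factor known from the design.

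**The reason for stratifying.** A reader might infer that the trial stratified because L-OS differs by site. The stated reason is only "to avoid imbalance in the distribution of the 2 groups at each site". That site predicts L-OS is an assumption, and the objection stands on this point.

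**Interval width.** It is tempting to say that the intervals without site are too wide and would shrink with adjustment. That is linear-model reasoning. Here the standard error of the log odds ratio rises when site is added (0.265 to 0.269, and 0.263 to 0.272). The objection stands.

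**Size.** The effect is small, in the safe direction, and close to simulation error for modest site differences. This also stands, and it sets the weight of the point.

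**Sparse data.** The Discussion reports no adverse effects after 13,433 treatments, and two of the five sites had not begun recruiting. Forcing site terms into the Poisson safety models could make them inestimable. That limits the fix.

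**Conclusion.** The point holds as a modest mismatch between design and analysis: site is a stratification factor and is not carried into the stated models. For assumed site L-OS rates spanning 10–30 % to 5–35 %, the cost is a test level of about 4.2–4.9 %, an odds ratio attenuated toward 1, and about 1 to 1.5 points of power. A larger loss (2.6 points) appears only at a between-site SD of 1.0 on the log-odds scale. With little or no site variation the effect is negligible.

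Two stronger readings fail. A reader might infer a raised false-positive risk, but omitting site did not inflate type I error in any setting examined. A reader might also infer that the trial is undersized, but 498 and 622 reproduce from the stated inputs, and adding site fits within the planned covariate allowance. The site rates, site shares and covariate effects used here are assumptions, because the article gives none.

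**What to change.** - **Primary model:** name site together with birth weight, gestational age and sex, either as four indicators or through stratified or conditional logistic regression. Use the same list in Sample size/Power analysis, Outcome measures for specific Aim 1 and Statistical analysis.
- **NEC and death:** do the same, specifying in advance Firth-penalised or site-conditioned logistic regression if events are sparse.
- **Poisson safety models:** leave them as they are, adding site only where counts allow.
- **Stated benefit:** describe it as a better calibrated test, a less attenuated odds ratio and a little power, without promising narrower log-odds-ratio intervals.

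The cost is four model terms against roughly 75 to 93 expected L-OS events, plus a rule for small site cells if a late-starting site enrols few infants. Sample size, data collection and trial conduct do not change.

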Our previous studies [69, 70] established feasibility for this technique and results were suggestive of immunostimulatory effects [70]. Recent research from other investigators suggest additional benefits including protection against ventilator-associated pneumonia, L-OS, NEC and clinical sepsis, an earlier attainment of full enteral feeds, enhanced maturation of oral feeding skills, improved growth, enhanced immune function, and improved breastfeeding outcomes [71–81]. An earlier attainment of full enteral feeds has been reported in several studies [70, 72, 76], and has important implications in terms of L-OS risk. When full enteral feeds are reached sooner, there is earlier removal of centrally placed venous catheters and intravenous parenteral nutrition, significantly reducing the infant’s risk for acquiring L-OS. Findings from these published reports suggest that oropharyngeal administration of mother’s milk may be beneficial for extremely premature infants. However, significant limitations, including small samples, retrospective analysis, and inconsistency in the technique, limit generalizability.

Published reports are primarily from small retrospective cohort studies, feasibility trials, studies in which oropharyngeal colostrum was included as part of a standardized feeding protocol, and a recent small (*n* = 48) RCT [71]. In published reports, investigators used various terms to describe ‘oropharyngeal administration of milk’ including oral care, mouth care, oral swabbing, oral colostrum and oral immune therapy. However, the underlying premise was the same, placing drops of mother’s milk (including early milk: colostrum) into the infant’s mouth so that biofactors may stimulate the infant’s oropharyngeal-associated lymphoid tissues, providing protective immunomodulatory effects [48].

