##### Oropharyngeal administration procedure

Using a standardized protocol, the nurse provides the dosing as follows: two syringes are warmed to room temperature. The first syringe’s cap is removed and the tip of the syringe is gently placed into the infant’s mouth, alongside the right buccal mucosal tissue. The syringe tip is directed posteriorly towards the oropharynx, and the total volume (0.1 mL) is slowly administered, over at least 1 minute. The second syringe is placed in the infant’s mouth in the same manner, but alongside the left buccal mucosal tissue. The entire volume (0.1 mL) is administered slowly, over at least 1 minute. A petite swab is used to carefully swab the right buccal mucosal tissue, followed by the left buccal mucosal tissue (≤5 seconds each side). A total volume of 0.2 mL is administered per treatment, with buccal swabbing taking place over 10 seconds. Vital signs are carefully monitored throughout the procedure. The procedure is repeated every 2 hours for 48 consecutive hours during the Initial Treatment Period, which begins within the infant’s first 96 hours of life. The Extended Treatment Period begins immediately after the Initial Treatment Period has been completed and ends when the infant reaches 32 weeks CGA as depicted in Fig. 2. Dosing is provided every 3 hours during the Extended Treatment Period. Participation in this study does not interfere with the initiation or progression of enteral feedings, which is left to the discretion of the attending physician. Urine, oral mucosal swabs, and stool specimens are collected from enrolled infants, and milk samples from their mothers, at specific time points, as depicted in Fig. 2.

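### Main models add mother's-milk feeding share, a post-randomisation variable, whenever it differs significantly between arms; if treatment has shifted it, the estimated effect is no longer the randomised one

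*Protocol article*

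**What the plan says.** Under Statistical analysis, the main approach is intention to treat. Logistic models for L-OS, NEC and death have group as the main independent variable and are adjusted for sex, gestational age and birth weight. The same paragraph turns to mother's milk given as feed. Because the amount "will affect our study endpoints, we will closely monitor and record the total amount of mother’s milk received", expressed as a percentage of total feeding volume. It states an expectation: "We do not anticipate the amount of milk the infant receives as an enteral feed will be affected by group assignment". It then gives the rule: "if we do observe a significant difference between the intervention and placebo groups, we will control for this variable in the regression models".

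The rule is not labelled a sensitivity analysis. The per-protocol analysis a few lines later is expressly called supplemental and exploratory, so the section does mark secondary analyses where it means to. As written, the rule governs the main models.

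Two other places bear on it. The Oropharyngeal administration procedure says that participation does not interfere with "initiation or progression of enteral feedings, which is left to the discretion of the attending physician". The Background says: "An earlier attainment of full enteral feeds has been reported in several studies [70, 72, 76], and has important implications in terms of L-OS risk". It also lists better breastfeeding results among the benefits reported elsewhere.

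**The concern.** Feeding share is not a baseline characteristic. It builds up during the hospital stay, while the infant is receiving milk or placebo and while illness and clinical decisions affect feeding. Randomisation balances what exists before allocation; it gives no protection when the model conditions on something measured later.

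The trigger adds to the difficulty. Adjustment happens only when the arms differ significantly. Chance apart, that is when allocation has moved the variable, and then two things can go wrong:

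- If feeding share carries part of the benefit, holding it fixed removes that part from the estimate.
- If illness severity drives both feeding share and L-OS, conditioning on feeding share makes infants with equal shares in the two arms differ in severity. This can produce an apparent effect where there is none.

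The choice of primary model would also depend on a test of post-randomisation data. At stake is whether the reported odds ratio for L-OS is the intention-to-treat effect that the section promises.

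**Working it through.** **1. The plan's own figure.** From Sample size/Power analysis: L-OS 20 % versus 10 %, two-sided alpha 0.05, power 80 %, 1:1 allocation, R² = 0.2. The logistic formula for a binary covariate, with overall risk P = 0.15 and B = 0.5, is

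n = [1.960·√(P(1−P)/B) + 0.842·√(0.2·0.8 + 0.1·0.9)]² / [(0.2 − 0.1)²·(1 − B)]

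= [1.960·√0.255 + 0.842·√0.25]² / 0.005 = 397.9.

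Dividing by (1 − 0.2) gives 497.4, hence the stated 498. The odds ratio is (0.1/0.9)/(0.2/0.8) = 0.444, as stated. The planning figure is sound, and 498 is used below.

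**2. The rule as simulated.** Feeding share is in SD units, and its mean differs between arms by a set shift. It enters the logistic model if the two-sample test gives |t| > 1.96. The protocol states no test or level, so 5 % two-sided is an assumption. The comparator is the same model without feeding share. The other covariates are left out, so the comparator has more than 80 % power at n = 498. All feeding and severity effects below are assumptions; the protocol gives none.

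**3. No true effect, shared cause.** Control risk is about 20 %. Illness severity is worth 0.7 log-odds of L-OS per SD and is correlated −0.5 with feeding share (sicker infants get less).

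| Arm shift in feeding share | Rule triggered | Odds ratio under the rule (truth 1.00) | Type I error |
|---|---|---|---|
| none | about 5–6 % | 1.00 | about 5 % |
| 0.2 SD | about 63 % | about 1.06 | about 5 % |
| 0.3 SD | about 92 % | about 1.11 | about 8 % |
| 0.5 SD | about 100 % | about 1.18 | about 10 % |

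Without feeding share the odds ratio stays at about 1.00 and the error at about 5 %. A correlation of +0.5 reverses the direction: for shifts of 0.3 to 0.5 SD the null odds ratio becomes about 0.91 to 0.84. Varying the strength of the shared cause (correlation −0.3 to −0.7, 0.5 to 1.0 log-odds per SD, shift 0.3 to 0.5 SD) gives null odds ratios from 1.05 to 1.39 and type I error from about 5 % to 27 %.

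**4. True benefit, same shared cause (correlation −0.5).** With an unadjusted odds ratio of about 0.41, the rule gives 0.45 (0.3 SD) to 0.48 (0.5 SD). Power falls from about 91 % to 83 % and 75 %.

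**5. True benefit, feeding share as mediator.** The total effect is set at the protocol's 20 % versus 10 % (odds ratio 0.444), with no shared cause.

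| Shift; log-odds of L-OS per SD of share | Odds ratio under the rule | Power under the rule |
|---|---|---|
| 0.2 SD; −0.3 | 0.457 | 84 % |
| 0.3 SD; −0.5 | 0.498 | 73 % |
| 0.5 SD; −0.8 | 0.618 | 40 % |

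The model without feeding share returns about 0.44, with power of about 87 % to 90 %.

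**The case against.** The strongest reply is that the rule may never do harm. The protocol expects no arm effect on feeding share. The study removes only 1.6 to 2.4 mL of milk a day, bedside staff are blinded, and milk from mothers in the placebo arm is kept for later feeds. If allocation leaves feeding unchanged, the rule is triggered in about 5–6 % of trials and causes no material bias. This stands. A reader might infer that the rule biases the L-OS estimate whatever happens, or that a significant difference proves feeding share is a mediator or collider. Neither follows.

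A reader might also take the Background as showing that the intervention acts through feeding share. It does not. It concerns time to full feeds: "When full enteral feeds are reached sooner, there is earlier removal of centrally placed venous catheters and intravenous parenteral nutrition". The rule concerns the composition of feeds. An infant can reach full feeds sooner with the same percentage of mother's milk. The earlier full feeds are findings from other studies, which the Background itself calls limited. With the reported breastfeeding results, this is indirect support only.

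A further tempting inference concerns the characteristics summarised under a baseline label, among them "duration [number of days] of central line placement and mechanical ventilation". These accrue after birth, so the label is loose. But no passage puts them in a model. The named covariates are sex, gestational age and birth weight, and the figure of up to 10 covariates is a power assumption. That these durations will be adjusted for is conjecture and forms no part of this point.

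What the reply does not do is justify the rule. Where feeding share is unaffected by allocation, adjustment is not needed to remove bias. Where it is affected, adjustment changes the quantity estimated.

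**Conclusion.** The concern holds in conditional form. The protocol lets a significance test decide whether a post-randomisation variable, which it says affects the endpoints, enters the main models for L-OS, NEC and death. If treatment or the care that follows it shifts feeding share, the randomised comparison is replaced by a conditional one that can lose part of the effect or show a false one. If the arms differ by chance only, there is no material bias.

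The range therefore starts at nil. In the shared-cause setting with correlation −0.5, a 0.2 SD shift leaves type I error at about 5 %, and a 0.5 SD shift takes it to about 10 % with a null odds ratio of about 1.18. Larger distortions need stronger assumptions. The direction cannot be known in advance: it turns on the sign of the relation between illness severity and feeding share, and pure mediation of a benefit pulls the estimate towards 1. The protocol fixes none of these inputs. The figures show that the rule can matter, not that it will. Since it concerns the primary analysis and costs nothing to remove, it should be changed before any arm comparison is seen.

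**What to change.** - Delete the significance-triggered adjustment from the main models.
- Fix the primary model as treatment, the pre-specified baseline covariates (sex, gestational age, birth weight) and the randomisation stratification factors (site and birth-weight stratum), whatever the feeding data show.
- Report mother's-milk share of feeding volume by arm, described as a post-randomisation variable.
- If its role is of interest, use it only in an analysis labelled exploratory, with feeding measured up to a fixed early landmark among infants still event-free at that time. Counting feeding up to each infant's first event would not do, because infants with events would have shorter windows and the exposure would depend on outcome timing.

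The cost is wording only. The data are already to be collected and no further infants are needed.
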